**DSHI-9***: Deliberate Self-Harm Inventory*	An initial question is asked whether someone has already intentionally injured his-/herself. If this is answered with yes, the type, onset, and frequency of self-harm are obtained [52].	1–6 items
**ISI***: Insomnia Severity Index*	Measures the quality of sleep and goes back to [53]. Difficulties falling asleep or staying asleep and the impairment they cause in everyday life are in the focus.	7 items
**SEED***: Short Evaluation of Eating Disorders*	It obtains the central symptoms of anorexia (underweight, fear of weight gain, impaired body awareness) and bulimia (binge eating, compensatory measures, excessive preoccupation with figure and weight) within the last month [54]. It has already been used in student samples with good experience.	6 items
**SFF***: Schutzfaktoren*	This short questionnaire captures three scales of protective factors that correlate significantly with data from the SDQ. Children who have more social, personal, and family resources are correspondingly less conspicuous in the SDQ [55].	12 items
**SISE:** *Single-Item Self-Esteem Scale*	This 1-item version goes back to the 10-item scale of the Rosenberg Self-Esteem Scale (RSES) developed by Rosenberg in 1965. The original sheet captured self-esteem with 5 positive and 5 negative questions. Recent studies have also demonstrated very good measurement properties for the 1-item version [56]. The question asks how well the statement “I have high self-esteem” applies to oneself. A 4-point Likert scale is then presented.	1 item
**CD-RISC-10:** *Connor-Davidson Resilience Scale-short form*	The long version was designed by Connor-Davidson in 2003 to measure resilience. Resilience means the ability to cope with internal or external stressors. The CD-RISC is widely used and has good psychometric properties (*a* = .84) [57]	10 items
**FAS III:** *Family Affluence Scale*	The FAS III measures the socioeconomic status using 6 questions and has very good quality criteria. Furthermore, the MacArthur scale question is connected, which asks about the subjective assessment of the prosperity of the adolescents’ own family [58]	6 items + 1

Finally, we will record demographic variables (e.g. age, gender) and socioeconomic status.

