### Sample size {14}

To analyse cluster-randomised trials, specific constraints must be followed, as individuals within a cluster are assumed to be more similar compared to individuals from different clusters. In order to detect significant effects, the sample size of the trial must be adjusted. This so-called clustering effect (1 + (*m*-1)×*p* [*m* = average number of subjects per cluster; *p* = intraclass correlation coefficient (ICC)]) resulted in an estimated *N* = 1795. For *m*, we assumed an average of 80 within an entire grade as the average class size in Germany varies nationwide (21.2–30.4 students per class), and the ICC was estimated quite conservatively at approximately 0.05 [70] on the basis of the primary outcome. Hence, a clustering effect of 4.95 was determined. Assuming a small effect size (Cohens *d* = 0.2) in universal prevention based on previous studies [71], with a significance level alpha = 0.05 and a power = 0.9, g*power suggests a total of *N* = 306 [72]. Considering the clustering effect, we have to multiply this by 4.95, reaching an overall *N* = 1515. Assuming a dropout rate of 25% due to moving out of the area, sickness, or other reasons, we must add another 379, leading to the final *N* = 1894.

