To assess protective factors for mental health in children and adolescents, we will use the German Scales for the Assessment of Protective factors (*Skalen zur Erfassung von Schutzfaktoren*) following the suggestions of Bettge and Ravens-Sieberer [55]. The scales have been validated in adolescents aged from 11 to 17 years and proved to be valid and practicable.

To measure non-suicidal self-injury (NSSI), we will use a shortened version of the nine-item *Deliberate Self-Harm Inventory* (DSHI-9), which was used in the SEYLE study. The original version of the DSHI [88] contains 17 items, and the DSHI-9 is an adaptation for adolescents [89]. To avoid confusing adolescents who do not harm themselves, we will introduce the questionnaire with a single question (“Have you ever hurt yourself with the intention of causing yourself physical pain?”). If they answer with “Yes”, NSSI will be explored further in terms of frequency, severity, and duration, using the DSHI-9. If they answer with “No”, NSSI will proceed to the next questionnaire. The internal consistency for the DSHI-9 lies between alpha = .66 and .85 [90].

In addition to demographic questions, the socioeconomic status will be captured using the *Family Affluence Sale* (FAS; [58] and the MacArthur Scale [91].

Finally, six questions regarding the COVID-19 pandemic will be asked, which explore stress factors, general mood, and well-being in families during the pandemic. These questions are from the Corona Health App, which was developed as part of a scientific cooperation between university partners, the Robert Koch Institute, and software companies (for detailed information, see www.corona-health.net).

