## Statistical methods

### Statistical methods for primary and secondary outcomes {20a}

The intervention group will be compared to the waiting list control group in terms of the difference in change. The data structure will be clustered at different levels (school type, school, grade, class, student), and we must take this into account. To check for the impact of levels, the ICC will be calculated. If the ICC is bigger than 0.1, we will analyse the data using (general) multilevel models. If not, mixed ANOVAS will be performed. First, a null model will be built consisting of the dependent variable and the random intercept. The model fit will be given using the Akaike information criterion AIC. Based on the null model, the independent variables of interest will be included, for the primary outcome self-perceived stress (measured with the PSS-10) and for the secondary outcomes the remaining measure (DERS-SF, SCS, ISI, PHQ-4, CD-RISC, SEED, DSHI-6, SISE, WHO-5, protective factors, FAS III). The AIC will be used to compare the models to one another.

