### Methods in analysis to handle protocol non-adherence and any statistical methods to handle missing data {20c}

If parts of the protocol need to be changed, this will always occur in consultation with the study management and the cooperation partners. The final decision on any changes will be made by the study management. Missing data should be minimised by the online survey. However, if this should occur, the procedure of multiple imputation will be chosen.

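### Self-injury is a lifetime yes/no question with frequency asked only after Yes, yet it falls under the same multilevel-or-mixed-ANOVA rule as the scale scores, with no score named

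*Protocol article*

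**What the plan says.** Section {20a} compares the arms on how much scores change. An ICC above 0.1 leads to (general) multilevel models; for any other value the text says "If not, mixed ANOVAS will be performed". The secondary outcomes are then named in one list, which ends "SEED, DSHI-6, SISE, WHO-5, protective factors, FAS III". No other model is given for any of them.

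The self-injury instrument is described twice. Table 1, under Secondary objectives, has an opening question and then: "If this is answered with yes, the type, onset, and frequency of self-harm are obtained". The Measures- questionnaire section words that opening question as a lifetime one, asking whether the student has at any time deliberately caused himself or herself physical pain. After a Yes, "NSSI will be explored further in terms of frequency, severity, and duration, using the DSHI-9"; after a No, the student moves to the next questionnaire. Both places call the instrument DSHI-9; {20a} calls it DSHI-6.

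Section {20b} lets the method depend on the type of variable, but only for subgroup comparisons. For missing data, section {20c} says "the procedure of multiple imputation will be chosen".

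**The concern.** A scale score such as the PSS-10 has a value for every student and a roughly continuous spread. Self-injury does not. Most students answer No and have either a blank or a zero for frequency; the rest are likely to have a long right tail. Mixed ANOVA, and equally a linear multilevel model, compares means, and the mean of such a variable depends heavily on a few very frequent self-injurers.

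There are two further difficulties. The article does not say whether the yes/no answer or the frequency is the outcome, so the choice could be made after the data are seen. And a lifetime question does not measure change over six months: a student who has once truthfully answered Yes must go on answering Yes.

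Self-injury is a named secondary outcome and a clinically serious one. A null result that came from the scoring or the recall period could be mistaken for evidence of no effect.

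**Working it through.** **1. Sizes from the article.** Section {14} states "with a significance level alpha = 0.05 and a power = 0.9", "Assuming a small effect size (Cohens *d* = 0.2) in universal prevention", and for cluster size "we assumed an average of 80 within an entire grade", with an ICC of 0.05 and 25% dropout. From its starting figure of 306:

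- design effect 1 + (80 − 1) × 0.05 = 4.95
- 306 × 4.95 = 1515
- 1515 × 0.25 = 379, and 1515 + 379 = 1894

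These steps reproduce. They are used here only to obtain sizes; whether 306 follows from d = 0.2 is a separate matter. Per arm they give 710 (1894 × 0.75 / 2), 757 (1515 / 2), and 153 once clustering is allowed for (1515 / 4.95 / 2). The article gives no prevalence, distribution, effect or power for self-injury, so everything below rests on assumptions.

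**2. Frequency against yes/no when only the share falls.** Assumed: relative reduction 30%, frequency log-normal with median 5, No coded as zero, one follow-up, clustering ignored, 710 per arm, two-sided 0.05, 3000 simulated trials per cell.

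| Control share | Mean frequency, log-SD 1.0 | Mean frequency, log-SD 1.5 | Yes/no share |
|---|---|---|---|
| 10% | 26% | 14% | 53% |
| 15% | 36% | 19% | 72% |
| 20% | 45% | 23% | 86% |

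Relative loss runs from 1 − 45/86 = 48% to 1 − 14/53 = 74%. At 153 per arm, frequency has 5–14% and yes/no about 16–29%.

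**3. The ranking reverses if only frequency changes.** With the same settings, but frequency halved among self-injurers and the share unchanged, mean frequency has 33–95% power at 710 per arm. The yes/no test has about 5%, which is its false-positive rate.

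**4. The group-by-time contrast that {20a} describes.** Assumed: share falling from 20% to 13%, median 4, log-SD 0.8–1.6, baseline/follow-up correlation 0.5–0.8, 1000 runs per cell. The comparator is a yes/no test stratified by baseline answer.

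- Frequency at 153 per arm: 6–20% against 36–52%, a loss of 59–85%.
- Frequency at 757 per arm: 15–71% against 96–100%, a loss of 29–84%.
- Frequency halved instead, 153 per arm: ANOVA on raw frequency has 10–37%, against 28–85% for a two-part test (yes/no plus log frequency among those with any), a loss of 54–70%.

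**5. If the yes/no answer is the score.** At one follow-up, ANOVA on 0/1 loses 0–6 percentage points against a binary test. In the group-by-time setting of step 4 it loses 22–35% at 153 per arm (worst cell 0.236 against 0.363) and 3–14% at 757, never half. The comparator there adjusts for baseline while the ANOVA uses change scores, so part of that gap is not due to the choice of ANOVA over a binary model.

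**6. The lifetime question.** Assume a share p of 10–20% answer Yes at baseline, 2–4% of the others start within six months, and the programme cuts onset by 30%. The follow-up share is p + (1 − p) × onset.

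- p = 0.10, onset 4%: 0.10 + 0.90 × 0.04 = 0.136 against 0.10 + 0.90 × 0.028 = 0.125, ratio 0.92
- p = 0.20, onset 2%: 0.20 + 0.80 × 0.02 = 0.216 against 0.20 + 0.80 × 0.014 = 0.211, ratio 0.98

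Both shares rise; neither can fall if answers are consistent. At 710 per arm a yes/no test of the follow-up shares has 6–9% power, and a test of new onset among baseline No has 12–22%, still ignoring clustering.

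**The case against.** The strongest reply is that the score, link function and skip coding of one secondary outcome among many belong in an analysis plan that is not shown. That would answer a complaint about missing detail. It does not answer this point, because {20a} does state a method, lists self-injury under it, and confines variable-dependent methods to subgroups.

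Second, the outcome list follows text about a null model with a random intercept and AIC, which is multilevel language, and the ICC of 0.05 was set for the primary outcome. This stands in part: which branch self-injury would take is unknown. But the phrase (general) multilevel models does not clearly mean a logistic or count model, and a linear one has the same difficulty.

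Third, step 2 compares two estimands under an effect that favours one of them. This stands, and step 3 shows it. The power loss is conditional and is not a general cost of ANOVA.

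Fourth, the yes/no test is itself weak at 153 per arm, so a null result could be expected from either method. This also stands.

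Finally, a reader might infer from {20c} that blanks after No will be imputed. The article does not say so. The skip is by design, {20c} speaks of missing data, and imputing the blanks is only its most literal reading. A sentence excluding them is a safeguard, not the correction of a stated error.

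**Conclusion.** The point holds in a limited form. A gated outcome with many zeros is placed under a rule built for scale scores, its score is not named, and its opening question cannot show a decrease within students.

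The size depends on the unnamed score. For frequency with zeros, and an effect on the share alone, about half or more of the power of a binary test can be lost: 48–74% in the single-follow-up runs, and 59–85% for the group-by-time contrast at the article's effective size. For the yes/no answer the loss is much smaller. Prevalence, skew, effect and onset rates are all assumed.

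Two stronger readings are tempting. One is that the stated method as such halves the power for self-injury; the article does not fix frequency as the score, so this does not follow. The other is that the trial would miss a clear fall in the share of students who self-injure; on the lifetime question as worded, no such fall can appear in consistent answers, whatever the model. For the same reason a logistic model on the unchanged question would not rescue the outcome. The change is worth making because it makes the result interpretable; it does not make self-injury a well-powered outcome.

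**What to change.** In {20a}, and where noted in {18a}, {20c} and Table 1:

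- Take self-injury out of the ANOVA/linear route.
- Name the score and tie it to the follow-up interval: any self-injury since the last assessment, or new onset among students who answered No at baseline. Word the online item at T2 and T3 to match.
- Analyse that yes/no score with a logistic mixed model with a random school intercept, and report the risk difference with its interval.
- Analyse frequency in all students with a negative binomial mixed model, coding No as zero. This model was not itself simulated above; it is proposed because it suits counts with many zeros and uses every student.
- State in {20c} that blanks created by the skip are zeros and are not imputed.
- Reconcile DSHI-6 in {20a} with DSHI-9 in Table 1 and the questionnaire section.

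The cost is a few sentences, one or two more model types to fit, and a clarified recall period in the online item. No extra assessment is needed.

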## Trial design {8}

The *LessStress* trial is designed as a cluster-randomised, controlled, non-blinded superiority trial with two parallel groups and a primary endpoint of self-perceived stress after 6 months. We will perform a random assignment on the school level with a 1:1 allocation ratio. The study will last for 6 months and will include four measurement time points: Pre = baseline, Post = student and teacher evaluation, T2 = 3-month follow-up, and T3 = 6-month follow-up (Fig. 1).

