## Assignment of interventions: allocation

### Sequence generation {16a}

Participating schools will be randomly assigned to one of the two groups using Microsoft Excel. The randomisation will be carried out on the school level following a 1:1 allocation ratio. This enables interference between the IG and WL to be avoided.

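### The only random term named for comparing change is an intercept; on repeated PSS-10 scores it cancels, so differences between schools in change go uncharged

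*Protocol article*

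**What the plan says.** All quotes are from the protocol article.

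- **Unit of randomisation** (Sequence generation, item 16a): "The randomisation will be carried out on the school level following a 1:1 allocation ratio". Trial design (item 8) says the same.
- **Contrast** (Statistical methods, item 20a): "The intervention group will be compared to the waiting list control group in terms of the difference in change".
- **Clustering** (same section): "The data structure will be clustered at different levels (school type, school, grade, class, student), and we must take this into account".
- **Choice of method** (same section): "If the ICC is bigger than 0.1, we will analyse the data using (general) multilevel models". The alternative is: "If not, mixed ANOVAS will be performed".
- **Model building** (same section): "First, a null model will be built consisting of the dependent variable and the random intercept". Then: "Based on the null model, the independent variables of interest will be included". AIC is the only rule given for comparing models.

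The section does not say at which level the intercept sits, or whether the dependent variable is the repeated PSS-10 score or a change score. It names no random slope for time and no school-by-time effect, and it excludes neither. Sample size (item 14) gives a planning ICC of 0.05 for the primary outcome, not for change in it.

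**The concern.** When schools are randomised and the question is whether PSS-10 changes differently between arms, the relevant noise is how much schools differ in their change. A random intercept captures how much schools differ in level. On repeated scores that level is the same at baseline and follow-up, so it subtracts out of the contrast. The test then treats students as independent for the quantity being tested.

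Schools can drift apart over six months for reasons unrelated to the programme, such as exam calendars or school climate. A test of this kind can read that drift as a programme effect. The primary comparison and every secondary comparison of change would have confidence intervals that are too narrow. The protocol enlarges the sample to allow for clustering, but this test would not use that allowance.

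**Working it through.** **Inputs from the protocol.** Cluster size m = 80, planning ICC 0.05, dropout 25%, total 1894 and alpha 0.05 (Sample size). The multilevel model is used only when the ICC exceeds 0.1 (Statistical methods).

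**Assumptions, not in the protocol.** CAC is the correlation of a school's true level between two waves. IAC is the same for a student within a school, taken as 0.5 below. There are 24 schools (1894/80 ≈ 23.7) with 59 completers each (1894 × 0.75 / 24 ≈ 59). The article says the number of schools cannot be predicted, and the 80 refers to one grade, so a school enrolling several grades would be larger.

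**Step 1. The plan's own clustering figure.** 1 + (80 − 1) × 0.05 = 4.95; 306 × 4.95 ≈ 1515; 1515 × 1.25 ≈ 1894. These products reproduce. Whether 306 is the right starting number is a separate matter and is not used here.

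**Step 2. Cancellation.** Write a score as school level + school-by-time deviation + student level + residual, with total variance 1 split as ICC × CAC, ICC × (1 − CAC), (1 − ICC) × IAC and (1 − ICC) × (1 − IAC). Follow-up minus baseline removes the school and student levels. What remains between schools is the school-by-time part, which an intercept-only random structure omits. A mixed model with school and student intercepts, fitted to simulated complete two-wave data, gave a group-by-time estimate of 0.00775 with SE 0.12850. An unclustered t-test on the students' change scores gave 0.00775 with SE 0.12850.

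**Step 3. Size, with student and school intercepts.**

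ICC of change = ICC(1 − CAC) / [ICC(1 − CAC) + (1 − ICC)(1 − IAC)]

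Type I error = 2 × {1 − Φ(1.96 / √(1 + (m − 1) × ICC of change))}

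Example with ICC 0.05, CAC 0.9, m = 59: 0.005 / (0.005 + 0.475) = 0.0104; 1 + 58 × 0.0104 = 1.604; 1.96 / √1.604 = 1.548; error 12.2%.

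| ICC | CAC | ICC of change | Error, m = 59 | Error, m = 80 |
|---|---|---|---|---|
| any | 1.0 | 0 | 5.0% | 5.0% |
| 0.05 | 0.95 | 0.0052 | 8.6% | 9.9% |
| 0.05 | 0.9 | 0.0104 | 12.2% | 14.7% |
| 0.05 | 0.8 | 0.0206 | 18.6% | 22.7% |
| 0.12 | 0.95 | 0.0135 | 14.2% | 17.2% |
| 0.12 | 0.9 | 0.0265 | 21.9% | 26.5% |
| 0.12 | 0.8 | 0.0517 | 32.7% | 38.5% |

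Simulation (24 schools, 59 completers, 4000 trials per setting) agrees: 8.5%, 13.3% and 18.7% at ICC 0.05, and 14.2%, 21.9% and 33.2% at ICC 0.12, for CAC 0.95, 0.9 and 0.8. A t-test on school mean changes with 22 degrees of freedom, on the same data, rejected in 4.5% to 5.7% of trials across all settings.

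**Step 4. School intercept only.** The model's error variance is now (1 − ICC) + ICC(1 − CAC), which wrongly includes stable differences between students. The true variance on the same scale is (1 − ICC)(1 − IAC) + m × ICC(1 − CAC). Their ratio replaces the square-root term in Step 3. At CAC 1.0 the ratio is 0.5 and the error 0.6%. At ICC 0.12, CAC 0.8, m = 59 it is (0.44 + 1.416) / 0.904 = 2.053 and the error 17.1%. At ICC 0.05, m = 59, the error is 1.5%, 2.9% and 6.3% for CAC 0.95, 0.9 and 0.8.

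**Step 5. The other readings.** A mixed ANOVA with only a student effect tests group-by-time against within-student residual variation, so for complete data Step 3 applies unchanged. If the dependent variable is the change score, a school random intercept is itself the school-specific change. Nothing cancels and the error is about 5%.

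**The case against.** The strongest reply is that the quoted sentence describes an empty model, the usual first step of a multilevel build, and not the final analysis. The section goes on to compare models and nowhere rules out a random slope. That stands: a reader might infer that the final model has only a random intercept, and the text does not support it. What can be said is that no other random term is named, the only additions described are independent variables, and AIC, the sole comparison rule, could drop a school-by-time term if one were tried.

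A second reply is that the outcome could be a change score, which would be sound. That also stands as a possibility. The wording leans the other way: the outcome is named as self-perceived stress on the PSS-10, and the alternative branch is mixed ANOVA, a repeated-measures method.

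Third, a reader might take a single range such as 12% to 33% as the size of the error. That would be overstated. CAC, IAC and the number of schools are assumptions; the error is 5% if schools do not differ in change, and a school-only intercept can be conservative. At the planning ICC of 0.05 the multilevel branch would not be run. The mixed ANOVA that replaces it has the same inflation if it carries only a student effect, so the switch does not protect the test.

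Finally, random-effect detail is often left to an analysis plan that is not shown here. That would answer a gap. This section, however, sets a contrast and a model-building recipe, and following the recipe literally on repeated scores gives wrong standard errors for that contrast.

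**Conclusion.** The concern holds in conditional form. If repeated PSS-10 scores are modelled with the random term the protocol names and no other, the test of difference in change leaves out between-school variation in change although schools are randomised. With student and school intercepts, or a mixed ANOVA with a student effect, type I error lies between about 5% and above 30%. With a school-only intercept it lies between about 1% and about 17% at 59 completers per school. Where it falls depends on how much schools differ in change and how many there are, and the protocol gives neither. The documents do not establish that the final model will be intercept-only. They do describe a route to a misleading primary test and nothing that closes it.

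**What to change.** In Statistical methods (item 20a), state the dependent variable and the level of every random effect, using one of two structures:

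1. PSS-10 change, or follow-up adjusted for baseline, with a school random intercept; or
2. repeated PSS-10 scores with a student intercept, a school intercept and a school-by-time random effect that stays in the model regardless of AIC.

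In either case, test the group contrast with small-sample degrees of freedom based on the number of schools (Satterthwaite or Kenward-Roger, about the number of schools minus 2). Use the same structure for the secondary outcomes.

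The cost is a sentence or two of analysis text and, under the second option, one more variance component. No extra data or students are needed. The small downside is a wider confidence interval when schools differ in change, which is the uncertainty the design carries.
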